### 10.2 Secondary study parameter(s)

As described in chapter 8.1 secondary study parameters will be postoperative complications, hospital readmission rate, 6-month mortality, the QoL of both patient and their informal caregiver (measured by using the WHOQoL-BREF), health related QoL of patients (measured using the EQ-5D-5L), burden on IC (using the CSI), the level of perceived SDM of the patient and their IC (using the CollaboRATE), perceived and preferred roles in DM of the patient and their IC (using the ACPS) and preferred participation in SDM of the patient and their IC (using the PICS). Continuous outcomes are analyzed using a linear regression model, whereas binary outcomes are analyzed by using a logistic regression model. Correction for important covariates (such as age,

gender, surgical history, comorbidities, use of medication, smoking status, use of alcohol, home situation) will take place. Hospital site will be a factor in the regression analysis. Repeated measures will be analyzed with mixed effect models with random effects per patients to address within patient clustering.

Lastly a cost-effectiveness analysis will be performed. The economic evaluation will include a cost analysis from hospital perspective, a cost-utility analysis from societal perspective (CUA, i.e. costs per QALY), and a budget impact analysis (BIA). In all three analyses, care with and without prehabilitation will be compared according to intention to treat. For the hospital cost analysis, 6 months interventions and stay will be assessed from the financial records of the Amphia Hospital, Meander Medical centre and Elisabeth TweeSteden hospital. For the CUA, also costs outside the hospital will be included, such as wound care, physiotherapy, home care, and informal care. These will be assessed using shortened versions of the iMCQ questionnaire (filled out at 6 months, over the preceding six months). Care will be valued according to Dutch reference prices, including travel costs. Productivity costs will not be included, because of the low labor participation in this 65+ study population. QALYs will be calculated using the Dutch tariff for the five-level EuroQoL EQ-5D (assessed at 0, and 6 months), with a sensitivity analysis using the EuroQoL visual analogue scale. Incremental average 6 months costs and QALYs will be compared using net-benefit analysis, with multiple imputation to account for missing data. The BIA will estimate the financial impact of different implementation scenarios at the national level. The analysis will be conducted from the perspectives of society, hospital and insurers, using the ZonMw BIA tool. The BIA will be based on the costs as estimated during the study, and the expected numbers of patients in the Netherlands. Healthcare will be valued according to cost prices (for the societal perspective) or NZa prices (for the hospital and insurer perspectives). Costs will be estimated per 1-year budget period for a time horizon of 5 years, assuming 50% to 100% implementation after 4 years.

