### 3. STUDY DESIGN

An RCT with a cost-effectiveness analysis, will be performed in three non-university large teaching hospitals in the Netherlands (Amphia Hospital Breda, Elisabeth Tweesteden Hospital Tilburg and Meander Medical Center Amersfoort), during the period of November 2025 to May 2028. All patients of 65 years or older, with a new onset of CLTI presented at the outpatient clinic of the vascular surgeon, who are planned for surgical or endovascular revascularization and who meet the in- and exclusion criteria are asked to participate in the study. In addition, their primary IC will also be requested to take part in the study. A primary IC is defined as follows: the person most involved in caring for the CLTI patient and supporting at least one instrumental activity of daily living of the patient or defined as the contact who supports in decisions by the patient. Patients can still be included, if their primary IC refuses participation. However, primary ICs can only be included together with a patient.

At the outpatient clinic information about the POCI-study is provided by a VNP or researcher and patients and ICs receive an information folder. They are called by telephone the next day by a researcher or VNP to ask if they want to participate. If so, oral informed consent will be obtained by the researcher or VNP and patients are randomized immediately upon inclusion, either into the prehabilitation group or the control group, the latter receiving the standard of care. Their IC will automatically be randomized to the same group. Within a few days all patients undergo a general health screening by a VNP or researcher and a blood sample will be taken as part of the standard care. Written informed consent will be obtained during this visit. Afterwards patients receive three questionnaires: the WHOQoL-BREF, the EQ-5D-5L and the iMTA Medical Consumption Questionnaire (iMCQ) (t=0). ICs are also asked to fill in two questionnaires: the WHOQoL-BREF, and the CSI (t=0). Afterwards, patients randomized into the intervention group are referred to the prehabilitation program where they are assessed by a physiotherapist and if indicated also a geriatrician, dietician or a quit smoking coach. The prehabilitation program will take two weeks, considering both the time needed to possibly reach significant results with the program and the time in which treatment is planned and must take place.

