#### 4.4 Sample size calculation

In this multicenter study we aim for a total of 300 patients, 100 patients from each hospital. With this sample size we have 80% statistical power to test hypotheses with 2-sided alpha set at 5% for the following differences between randomized groups.

Length of hospital stay: The calculation of the effect size is based on the difference in means with SD. In a previous study (7), prehabilitation was associated with a difference of 2 vs over 4 days on average. A halving in length of stay requires 54 patients in total (27 per group, assuming a SD of log (LOS) of 0.9, as in the previous study). With 300 patients, a decrease by a factor 0.75 (so 25% reduction in LOS) provides 80% power.

For complications, we will analyze minor and major complications. In the previous study (7), prehabilitation was associated with the following reductions in complications: minor, 26 vs 14%; major 23 vs 18%. These differences would require sample sizes of 346 and over 2000 patients in total respectively. With 300 patients we will have reasonable power for detecting a difference in minor complications (power 69%), but insufficient statistical power for a difference of 23 vs 18% in major complications (power 15%). These calculations were done using the online sample size calculators at <https://sample-size.net/>

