#### Follow-up at 6 months

At 6 months after revascularization we will again ask patients and their ICs to fill in the WHOQOL-BREF. Patients are also asked to fill in the EQ-5D-5L questionnaire and the iMCQ. The IC is also asked to fill in the CSI. In addition, both patient and IC are asked to fill in an additional questionnaire regarding process evaluation.

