## 10. STATISTICAL ANALYSIS

Statistical analyses are performed using IBM SPSS statistical software (SPSS Inc., Chicago, Illinois, USA). A two-sided p-value of less than 0.05 will be considered statistically significant. Adjusted analysis with prognostic baseline characteristics (e.g. gender, age) will be performed using regression analysis. This analysis corrects for baseline differences, optimizes statistical power, and provides better individualized treatment effect estimates. Missing data will be studied for specific patterns of occurrence, and multiply imputed. A power analysis with sample size calculation is performed, as described in paragraph 4.4 (sample size calculation).

Results of categorical data variables are described in frequencies with percentages and differences will be tested using the Chi-square test. Continuous data are described as median (interquartile range) and Mann-Whitney U-tests will be performed to test for group differences. Ordinal variables will be tested using the Mann-Whitney U-test. Data analysis will be done according to the intention-to-treat concept, which implies that all patients are included in the analysis irrespective of whether they completed the prehabilitation program. Secondary, a per protocol analysis will be performed, although interpretability may be difficult for this analysis. All epidemiological issues and statistical methods will be discussed with [name]. [name], a member of the research group.

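### Section 10.2 does not give the t=0 score a role in the 6-month quality-of-life and caregiver-strain comparisons, so the models it names may be less precise than the collected data allow

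*Protocol*

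**What the plan says.** Protocol section 3 has patients complete the WHOQoL-BREF and EQ-5D-5L (with the iMCQ) at the screening visit. For informal caregivers it states: "ICs are also asked to fill in two questionnaires: the WHOQoL-BREF, and the CSI (t=0"). The same instruments return once, at 6 months. Under section 8.3, Follow-up at 6 months: "At 6 months after revascularization we will again ask patients and their ICs to fill in the WHOQOL-BREF", with the EQ-5D-5L for patients and the CSI for caregivers. Each score therefore has one t=0 value and one later value.

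Section 10.2 gives the models: "Continuous outcomes are analyzed using a linear regression model, whereas binary outcomes are analyzed by using a logistic regression model". Eight example covariates follow (age, gender, surgical history, comorbidities, medication, smoking, alcohol, home situation), with hospital site as a factor. They are the same eight that section 10.1 lists for length of stay, an outcome that has no baseline value. The section then says: "Repeated measures will be analyzed with mixed effect models with random effects per patients to address within patient clustering".

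Section 10 sets a general rule of adjusting for prognostic baseline characteristics, with gender and age as examples, and says this is meant to correct for baseline differences and gain power.

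**The concern.** A 6-month WHOQoL-BREF, EQ-5D-5L or CSI score is both a continuous outcome and a repeated measure, so section 10.2 covers it twice. It does not say which model gives the reported result, whether the t=0 score enters as a covariate or as an outcome, or whether the mixed model has an arm-by-time term. The models that fit the wording do not perform alike:

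- Linear regression on the listed covariates compares 6-month scores and ignores t=0.
- A random-intercept model with arm-by-time and separate baseline means per arm is a change-score analysis.
- A model with one arm effect over both occasions averages the 6-month effect with an occasion before the programme, where no programme effect can exist.
- Linear regression with the t=0 score added, or a mixed model with a common baseline mean and arm-by-time, is the baseline-adjusted comparison.

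The protocol summary singles out quality of life as the clinical outcome to improve besides length of stay, and section 4.4 gives it no power calculation. Its precision therefore rests on the choice of model.

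**Working it through.** **The plan's own figure.** The protocol has no power figure, SD or correlation for quality of life or CSI. The only calculation for a continuous outcome is for length of stay: "With 300 patients, a decrease by a factor 0.75 (so 25% reduction in LOS) provides 80% power". With 150 per arm (300 in total; equal allocation assumed from the 27 per group in section 4.4), SD of log length of stay 0.9 and two-sided 5%:

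- difference = |ln 0.75| = 0.288
- standard error = 0.9 × sqrt(2/150) = 0.104
- power = Φ(0.288/0.104 − 1.96) = 79.1%, in line with the stated 80%.

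**Inputs for this point.** Two-sided 5% is from section 10. The correlation rho between the t=0 and 6-month scores is not in the protocol and is assumed at 0.3, 0.5 and 0.7. Further assumptions are equal SD at both occasions, no other covariates and complete data.

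**Relative variance of the estimated 6-month difference**

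- 6-month score only: 1
- change score (arm-by-time, free baseline means): 2(1 − rho) = 1.40, 1.00, 0.60
- baseline-adjusted: 1 − rho² = 0.91, 0.75, 0.51
- mean of both occasions: (1 + rho)/2 = 0.65, 0.75, 0.85, for an effect that is half the 6-month effect.

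Against the 6-month score alone, baseline adjustment cuts variance by rho² = 9%, 25%, 49%. Against the change score the ratio is (1 + rho)/2, a cut of 35%, 25%, 15%.

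**Power.** An analysis with 80% power has noncentrality 1.960 + 0.842 = 2.802. Another analysis of the same effect has power Φ(2.802 × sqrt(variance ratio) − 1.96). At rho 0.5 against the 6-month score, for example, 2.802 × sqrt(1/0.75) = 3.235, and Φ(1.275) = 90%.

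| rho | Baseline-adjusted, where 6-month score alone has 80% | Baseline-adjusted, where change score has 80% |
|---|---|---|
| 0.3 | 84% | 94% |
| 0.5 | 90% | 90% |
| 0.7 | 97.5% | 86% |

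Conversely, where the baseline-adjusted analysis has 80%, the 6-month score alone has 76%, 68%, 52% and the change score 62%, 68%, 73%. These ratios do not depend on the sample size.

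**Mixed-model forms.** Generalised least squares was run with a known random-intercept covariance and 150 per arm, scaled so that the baseline-adjusted analysis has 80% power (rho 0.3, 0.5, 0.7):

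- common baseline mean and arm-by-time: full effect, power 80% throughout, no loss
- arm-by-time with free baseline means: full effect, power 62%, 68%, 73%
- one arm effect over both occasions: exactly half the 6-month effect, power 38%, 29%, 19%.

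**The case against.** The strongest reply is that nothing in the protocol excludes the t=0 score. Both covariate lists are introduced as examples, and the general rule in section 10 is one that a t=0 score fits in kind and in purpose. The list in section 10.2 also serves binary outcomes and the shared-decision scales, which have no t=0 value, so an instrument-specific baseline would not be expected in it. This stands: the plan leaves the t=0 score unnamed, and it would be wrong to say that it omits it.

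Second, the structure of the mixed model is not stated. A reader might infer that the plan treats t=0 merely as a second outcome and will report an effect diluted by half. The protocol does not support that. It never states a single arm effect over both occasions, and a model with t=0 as an outcome, a common baseline mean and arm-by-time loses nothing. What remains is that the wording does not rule the diluted form out.

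Third, detailed model terms for secondary outcomes often go into a statistical analysis plan, which is not at hand. That limits the weight of the point. But section 10.2 already names models and covariates, and it places the same scores under two models without saying which one is reported.

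Fourth, the size depends on an assumed correlation. The relevant quantity is the correlation that remains after the other covariates, which may be smaller. This also stands, and no single loss in percentage points should be quoted.

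Fifth, patients are randomised on inclusion and complete t=0 later, unblinded (sections 3 and 8.2). Knowing the allocation could shift t=0 answers. Baseline adjustment would carry about rho times such a shift into the result, a change score all of it, and the 6-month score alone none. This is a real cost of the fix.

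**Conclusion.** The point holds as a gap in specification that puts precision at risk, not as an error in the plan. Comparisons of follow-up scores and of change scores are both valid under randomisation. What may be lost is efficiency on secondary outcomes that have no power calculation. Over an assumed rho of 0.3 to 0.7 without other covariates, naming the t=0 score raises power from 80% to between 84% and 97.5% against the 6-month score alone, and from 80% to between 94% and 86% against the change score. If the mixed model already planned has a common baseline mean and arm-by-time, there is no loss. Halving of the effect would arise only under a model that the protocol does not state. The number of caregivers and of patients answering at 6 months is not given, so absolute power cannot be computed.

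**What to change.** Add to section 10.2 a statement with this content: for WHOQoL-BREF, EQ-5D-5L and CSI, the 6-month scores are compared between arms with adjustment for the t=0 score of the same instrument and for hospital, besides the covariates already listed. This can be done by analysis of covariance or, equivalently, by a mixed model with a common baseline mean and an arm-by-time term. The reported effect is the difference between arms at 6 months.

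Because t=0 is completed after open-label randomisation, though before the programme, also state that t=0 scores will be checked for imbalance between arms and that an analysis without the t=0 score will be given as a sensitivity analysis.

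The cost is a few sentences and one extra analysis per score. No new data are needed. Missing t=0 scores would fall under the multiple imputation already planned in section 10.

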**Nature and extent of the burden and risks associated with participation, benefit and group relatedness:** The burden for all participants consists of the visit to the MVE, drawing a blood sample and filling in questionnaires at baseline, at the second visit to the vascular surgeon and 6 months after revascularization. Patients in the intervention group are provided with home-based exercises by a physiotherapist. These exercises take time and should be performed daily and written down in a diary. If indicated they also receive dietary advice and advices from the geriatrician to take into account at home.

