After treatment planning is complete, the vascular surgeon will discuss this plan with patients and their IC in a second visit to the outpatient clinic. Afterwards both patient and IC are asked to fill in three questionnaires, regarding the SDM process: the CollaboRATE, the ACPS and the PICS (tSDM=0).

Patients and their ICs will be included during a period of 2 years and will stay in follow-up for 6 months. At the 6-months follow-up patients are asked to fill in four questionnaires: the

WHOQoL-BREF, the EQ-5D-5L, the iMCQ and a process evaluation form designed by the researchers (t=1). ICs are asked to fill in three questionnaires: the WHOQoL-BREF, the CSI and a process evaluation form (t=1).

Inclusion of the patient and their IC will be on the day after the first outpatient clinic visit. This way the prehabilitation starts within a few days, parallel to the treatment planning (imaging, multidisciplinary meeting, planning for surgery or endovascular treatment) and there will be no delay in the treatment schedule.

FIGURE 1 – FLOWCHART POCI-STUDY

[figure not shown]

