## 5. TREATMENT OF RESEARCH PARTICIPANTS

In this study we will provide a multidisciplinary prehabilitation program to patients that are planned to undergo endovascular or surgical revascularization for CLTI. The duration of the prehabilitation program is at least 2 weeks and consists of seven major components:

- 1) Screening of general health, signs of frailty, comorbidities, nutritional state, and performing functional and cognitive testing, by a vascular nurse practitioner or researcher at the MVE.

All patients included in the study, regardless of control or intervention group, will go through this first step of the MVE. Afterwards the patients in the intervention group start their prehabilitation program, consisting of:

- 2) Screening and provision of personalized, home-based exercises by a physiotherapist. Patients will track their daily activities in a diary.

And, if indicated:

- 3) Provision of nutritional advice by a dietician, based on the body mass index (BMI), Mini Nutritional Assessment Short Form (MNA-SF) score and the SNAQ-score. If indicated, patients will receive high protein nutrient drinks and recommendations of a high protein diet.
- 4) Comprehensive geriatric assessment (CGA) by a geriatrician.
- 5) In case of an iron deficiency anemia (haemoglobin <8,1 mmol/L for male patients and <7,4 mmol/L for female patients), patients will receive iron infusion using ferric carboxymaltose,
- 6) Assessment of self-reliance and home situation by a prearranged homecare nurse
- 7) Guidance and support for smoking cessation by a quit smoking coach.

The IC participates with the patient in the program. We performed a pilot interview study in CLTI patients and their ICs. Their advises and recommendations are incorporated in our prehabilitation program for CLTI and the POCI-study in general.

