#### Clinical admission

At the time of admission, after +/- 2 weeks, a process analysis will be performed by using a process evaluation form designed by the researchers (F1-Vragenlijsten). We will test compliance and evaluate whether the given interventions and/or instructions were performed at home. Patients diaries are used as a guideline throughout this evaluation.

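### The six-month iMCQ look-back starts at revascularisation, so out-of-hospital prehabilitation costs fall in neither questionnaire window

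*Protocol*

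**What the plan says.** - **Last assessment.** Section 8.3 (Follow-up at 6 months) states: "At 6 months after revascularization we will again ask patients and their ICs to fill in the WHOQOL-BREF". For the same occasion it adds: "Patients are also asked to fill in the EQ-5D-5L questionnaire and the iMCQ". The Summary gives the same anchor for the questionnaires: "filling in questionnaires at baseline, at the second visit to the vascular surgeon and 6 months after revascularization".
- **iMCQ recall.** Section 10.2 takes care outside the hospital (wound care, physiotherapy, home care and informal care are its examples) from "shortened versions of the iMCQ questionnaire (filled out at 6 months, over the preceding six months".
- **Baseline iMCQ.** Section 3 has patients receive it at t=0, after the health screening and before referral to the prehabilitation programme.
- **Length of the programme.** Section 5: "The duration of the prehabilitation program is at least 2 weeks". Section 8.3 (Clinical admission): "At the time of admission, after +/- 2 weeks, a process analysis will be performed".
- **QALYs.** Section 10.2: "QALYs will be calculated using the Dutch tariff for the five-level EuroQoL EQ-5D (assessed at 0, and 6 months". Costs and QALYs are then compared as six-month averages, according to intention to treat.
- **Hospital costs.** Section 10.2 takes these from the hospitals' financial records over six months and does not say when the six months begin.
- **Follow-up in the design section.** Section 3 says only that patients "will stay in follow-up for 6 months", with no starting point.

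**The concern.** The economic evaluation has to include what the intervention itself consumes. Several components in Section 5 may generate care outside the hospital: physiotherapist-prescribed home exercises, a homecare nurse's assessment, and the involvement of the informal caregiver. The iMCQ is the only named source for physiotherapy, home care and informal care outside hospital. If its window opens only when the programme has ended, that resource use is lost, mainly in the arm that generates it.

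The budget impact analysis is built on the costs estimated in the study, so the omission would pass into the national five-year figures. The planned multiple imputation cannot repair it, because the period is missing for every patient by design. Recall wording and assessment dates are data collection, so a later analysis plan could not recover the information either.

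**Working it through.** The protocol states no figure for this point, so there is none to reproduce. The check is arithmetic on the timeline.

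**Inputs**
- Recall of the last iMCQ: six months = 6 × 365.25/12 = 182.6 days (Section 10.2).
- Date of the last iMCQ: six months after revascularisation (Summary; Section 8.3).
- Wait from baseline to revascularisation, *w*: the protocol says at least, or about, two weeks. I take 14 days as the reference and assume a range of 10 to 42 days.

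**Step 1: what each questionnaire covers.** With revascularisation on day *w* after baseline, the last iMCQ falls on day *w* + 182.6 and looks back to day *w*. The baseline iMCQ covers time up to day 0. Days 0 to *w* are in neither window, and the programme runs in those days.

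**Step 2: share of the horizon missed, and the time spanned by the EQ-5D.** The EQ-5D is taken at t=0 and at the last assessment.
- Share missed by the iMCQ = *w* / (*w* + 182.6)
- EQ-5D span in years = (*w* + 182.6) / 365.25
- iMCQ span in years = 182.6 / 365.25 = 0.500

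| *w* (days) | Share missed | EQ-5D span (years) | iMCQ span (years) |
|---|---|---|---|
| 10 | 5.2% | 0.527 | 0.500 |
| 14 | 7.1% | 0.538 | 0.500 |
| 21 | 10.3% | 0.557 | 0.500 |
| 28 | 13.3% | 0.577 | 0.500 |
| 42 | 18.7% | 0.615 | 0.500 |

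At *w* = 14: 14/196.6 = 7.1% and 196.6/365.25 = 0.538. Whatever the value of *w*, the missed stretch contains the whole programme period.

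**Step 3: effect on incremental cost.** Write the programme cost per intervention patient as A (delivered outside hospital) plus B (delivered by the hospital).
- If the financial records are read from randomisation, B is captured and programme cost is understated by A.
- If they are read from revascularisation, it is understated by A + B.

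The protocol gives neither A nor B, so no amount can be stated. For A the direction is clear: the loss falls on the intervention arm. Other care used while waiting is missed in both arms, and its net effect is unknown.

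**Step 4: effect on QALYs.** The wait lies inside the EQ-5D interval. At assumed utilities of 0.5 to 0.7, 14 days are worth 0.5 × 14/365.25 = 0.019 to 0.7 × 14/365.25 = 0.027 QALY per patient. This is counted in both arms and largely cancels if the waits are equal. The fault here is the mismatch with the cost window.

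**Step 5: patients without a date.** A patient who is never revascularised has no day from which to count the last assessment, yet Sections 10 and 10.2 promise an intention-to-treat analysis.

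**The case against.** The best defence has four parts.

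- **Hospital-delivered components may be captured.** The clinic screening, the iron infusion given as a day-care admission and probably the geriatric assessment can appear in the financial records. This stands. A reader might infer that all programme costs are lost, but the protocol does not support that: the start of the record window is open, and the iMCQ is named only for costs outside hospital. What is clearly outside hospital is fairly narrow: the homecare nurse, informal care and any community physiotherapy.
- **The wait need not differ by arm.** Section 3 says prehabilitation runs alongside treatment planning and that no delay is intended. This also stands. A reader might infer a wait that depends on treatment and so damages the randomised comparison, but no waiting time by arm is given. Control patients with rest pain or tissue loss may also use care while waiting.
- **The clock may run from inclusion.** Two years of inclusion plus six months of follow-up fills November 2025 to May 2028 (24 + 6 = 30 months), and Section 10.2 speaks of 0 and 6 months. This shows that the protocol points to two clocks. It does not remove the explicit anchor at revascularisation in the Summary and Section 8.3, the only places that give the questionnaires a starting point.
- **Equal recovery time.** Measuring quality of life six months after the procedure gives every patient the same recovery period. That is a fair reason to keep the visit where it is, and the fix below does so.

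**Conclusion.** The point holds in a limited form. Followed as written, the two iMCQs leave out the period from baseline to revascularisation. Out-of-hospital programme care is then uncollected, mainly in the intervention arm, and for those costs the incremental societal cost is understated in favour of prehabilitation. At a 14-day wait the gap is 7.1% of the horizon and the whole programme period; over the assumed 10 to 42 days it is 5.2% to 18.7%. The EQ-5D and iMCQ spans differ by the same wait (0.538 against 0.500 years at 14 days), although both are labelled six months.

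The size in money is unknown, and a net bias of the whole economic analysis is not shown. Three further readings go beyond the text:
- Deaths before revascularisation are not shown to be lost, because no section ties six-month mortality to revascularisation and mortality is taken from the patient dossier.
- QALYs during the wait are not left out, because the EQ-5D interval includes them.
- Patients who lose the limb or die after revascularisation do have a date for the last assessment; only those never revascularised lack one.

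The primary outcome, length of stay, is not affected. This should be fixed, but it concerns one secondary outcome.

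**What to change.** 1. Word the recall of the last iMCQ as running since inclusion, in place of the preceding six months.
2. Record out-of-hospital programme use directly from trial records: referrals and the patient diaries, which the protocol now uses only to check compliance.
3. State that the hospital-record cost window and the QALY calculation both start at randomisation, and compute both over actual dates.
4. For patients never revascularised, set the last assessment at a date counted from randomisation.
5. State the starting point of the six-month follow-up in Section 3 so that it agrees with the Summary and Section 8.3.

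The cost is wording, a questionnaire instruction and a small addition to the case record form. The recall period becomes a few weeks longer. Moving every six-month outcome to a clock from randomisation is not required and would give up equal recovery time after the procedure. The changes to recall and recording need to be in place before data accrue, because resource use that was never asked about cannot be reliably recovered.

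### Out-of-hospital and informal care in the roughly two weeks before revascularisation falls outside both iMCQ recall periods, while QALYs are measured from t=0

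*Protocol*

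**What the plan says.** Protocol Section 10.2 defines the societal cost-utility analysis (CUA) so that it reaches beyond the hospital: "For the CUA, also costs outside the hospital will be included, such as wound care, physiotherapy, home care, and informal care". The source it names for these items is "shortened versions of the iMCQ questionnaire (filled out at 6 months, over the preceding six months". QALYs in the same analysis come from the "EuroQoL EQ-5D (assessed at 0, and 6 months", and incremental six-month costs and QALYs are then combined in a net-benefit analysis.

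Two places fix when the six-month forms are completed. Section 8.3, under the follow-up heading, says "At 6 months after revascularization we will again ask patients and their ICs to fill in the WHOQOL-BREF" and continues "Patients are also asked to fill in the EQ-5D-5L questionnaire and the iMCQ". The Summary sets the questionnaires at baseline, "at the second visit to the vascular surgeon and 6 months after revascularization". Section 3 says only that participants "will stay in follow-up for 6 months", without naming a starting point.

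The first iMCQ is given at t=0, at the screening visit. Section 3 then goes on: "Afterwards, patients randomized into the intervention group are referred to the prehabilitation program where they are assessed by a physiotherapist". Section 3 gives the programme two weeks, Section 8.3 about two weeks, and Section 5 and the Dutch summary at least two weeks, in each case before the procedure.

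**The concern.** A six-month recall that ends six months after revascularisation starts at about revascularisation. The t=0 form looks back from a point before the intervention arm enters the programme. The weeks between the two belong to neither form, and they are the weeks in which the arms are designed to differ. In that period the intervention arm does home exercises, may be assessed by a homecare nurse, and involves the informal caregiver (Section 5).

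Two things are at stake. First, the societal CUA may leave out part of the care used during prehabilitation itself. Second, costs and QALYs in one net-benefit analysis would rest on different periods. The budget impact analysis uses the costs estimated in the study, so a gap could carry into its societal perspective. Multiple imputation, which Section 10.2 plans for missing data, does not help with a period about which no patient was asked.

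**Working it through.** The protocol gives no figure to reproduce here, so the check is to lay the measurement periods on one time axis.

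**Inputs**
- Follow-up iMCQ and EQ-5D-5L: six months after revascularisation (Section 8.3; Summary). Six months is taken as 183 days.
- Recall of the follow-up iMCQ: the preceding six months (Section 10.2).
- First iMCQ and EQ-5D-5L: t=0, before referral to the programme (Section 3).
- Interval from t=0 to revascularisation, g: about 14 days (Sections 3 and 8.3; Section 5 has this as a minimum). The protocol gives no separate interval for control patients. I assume a similar one, because Section 3 says prehabilitation runs alongside treatment planning without delaying it.

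**What is recorded between t=0 and revascularisation**
- Second outpatient visit: the three shared decision-making questionnaires only (Sections 3 and 8.3).
- Admission: a process evaluation described as testing compliance, guided by the patient diary (Section 8.3).
- Diary: the patient's own activities (Sections 5 and 8.3).
- Caregiver Strain Index: t=0 and six months only; it measures strain, not hours of care.
- Hospital financial records: care delivered in the hospital. Section 10.2 does not say when their six months begin.

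None of these is described as recording community care or caregiver hours, and Section 10.2 links none of the forms or the diary to costing.

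**Size of the gap**

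Uncovered share = g / (g + 183).
- g = 14: 14 / 197 = 7.1%
- g = 21 (assumed): 21 / 204 = 10.3%
- g = 28 (assumed): 28 / 211 = 13.3%

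Only the first line rests on the planned interval. The other two apply only if patients wait longer than planned.

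**Spans compared at g = 14**
- EQ-5D assessments: 197 / 365 = 0.54 years.
- Out-of-hospital costs from the follow-up iMCQ: 183 / 365 = 0.50 years.

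These are shares of calendar time, not of cost. The protocol gives no unit costs or caregiver hours, and patients may take part without a caregiver (Section 3), so a cost effect cannot be computed.

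**The case against.** - **The anchor may be t=0.** Section 10.2 uses one nominal six-month horizon for costs and QALYs. The study calendar in Section 3 (November 2025 to May 2028, about 30 months) fits two years of inclusion plus six months counted from inclusion. This is weak evidence, because the calendar is approximate. The two places that name a starting point both say revascularisation, and nothing names a different one. If t=0 is meant, those two places need correcting instead.
- **Other records may fill the gap.** This largely stands for programme items. Screening, physiotherapist, geriatrician and dietician assessments and the day-care iron infusion can be counted from hospital or programme records. So can the homecare nurse assessment, as a named programme component. The questionnaire appendix is not shown, so the admission form may ask more than its description suggests.
- **The t=0 iMCQ gives a rate of usual care** that could be carried over two weeks in both arms. That is a fair approximation for usual care, but it cannot pick up caregiver time that the programme itself creates.
- **Costing windows belong in an analysis plan.** In part they do. Here, however, the protocol fixes the timing and the recall of the form, and a later plan cannot recover answers to a question that was not asked.

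A reader might infer that the cost of prehabilitation as a whole is missing, or that the CUA is biased in its favour. The documents support neither. Most programme items can be traced, usual out-of-hospital care goes unrecorded in both arms, and the arm-specific remainder is of unknown size.

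**Conclusion.** The point holds in a limited form. As the protocol describes the forms, out-of-hospital and informal care between t=0 and revascularisation falls in neither iMCQ recall period, while the EQ-5D spans that time. At the planned interval this is about 14 of 197 days, or 7%. The likely loss is mainly informal caregiver time and community care. The size and the net direction of any bias in the societal CUA are unknown.

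This rests on three assumptions: the revascularisation anchor is meant as written, the interval is close to two weeks, and the forms that are not shown do not already ask about care use in this period. It is a minor correction to a secondary economic analysis; the primary endpoint, length of stay, is untouched.

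**What to change.** In Sections 10.2 and 8.3, state one horizon: hospital costs, out-of-hospital costs and QALYs all run from t=0 (hospital costs from randomisation) to six months after revascularisation. Word the six-month iMCQ so that patients in both arms report care, including informal care, since t=0 rather than over the preceding six months.

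This needs no extra form or visit. The cost is a recall of about 197 instead of 183 days, with slightly more recall error. A short iMCQ at admission for revascularisation, given to both arms, would avoid the longer recall. It is optional and adds one form per patient (about 300) in a protocol that aims to keep questionnaires brief. Either change has to be in the forms before patients complete them.
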